## Discussion

Sensory and motor nerve function improvement following LDH, especially the influence on time and the quality of recovery, are infrequently subjected to well-designed clinical trials. There is a need for data with validated modern outcome instruments to assess evidence-based prognosis for patients with sensomotoric dysfunction. The results of this study will detect the effect of EMG-triggered multichannel SES on the improvement of mechanical and thermal sensitivity and the effect on motor recovery and pain, associated with clinical and laboratory parameters. Furthermore, additional influencing factors on sensomotoric recovery may be identified and will hopefully lead allow treatment recommendations for patients with LDH accompanied by a sensomotoric deficit.

To guarantee a high scientific value, the outcome instruments used in this trial are adjusted to the latest standards in the literature among spinal and neurologic investigations. The QST is a valuable instrument for the objectification of sensory function [25, 34]. The MMT also depicts a highly valuable tool for the quantification of muscle power and therefore we utilize the possibility to avoid an investigator’s bias, not considered in most of the previous trials. Our patient’s self-assessment (ODI, EQ5D, COMI, PD-Q, BDI) matches the highest standards of the middle European assessments for quality of life and consequently subjective efficacy of spinal procedures and management options. Patients are treated in a standardized manner and are therefore well comparable. All quantitative values can be compared between the initial treatment groups (conservative or operative) as well as between the therapy groups (SES or non-SES) and, additionally, within each patient by collecting and comparing data bilaterally (affected and non-affected side). Furthermore, our SES program was developed with leading clinical specialists and therefore matches the latest standards and innovations. Devices are especially programmed so that after the scheduled application of the medical device, individual usage times and thresholds can be read and considered by the clinical investigators.

Limitations of our trial include the expected cross-over from group conservative to group operative, as recruitment may prevail in favor of surgically treated patients. Furthermore, patients initially treated medically and randomized to the group receiving SES, will start the surgical treatment with potentially already influenced sensomotoric function. Nevertheless, before the operation a QST will be done and values will provide as reference.

Altogether, our trial was designed responsibly by experienced investigators from diverse specialties and is expected to deliver highly qualitative results in the first prospective clinical trial investigating the influence of EMG-triggered SES on the sensory and motoric recovery in patients suffering from LDH. Additionally, we expect to supply relevant outcome data on both conservative and operative management to prospectively identify a superior treatment method for symptomatic LDH.

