**Discussion:**

The results of the RECO study will detect the effect of EMG-triggered multichannel SES on the improvement of mechanical and thermal sensitivity and the effect on motor recovery and pain, associated with clinical and laboratory parameters. Furthermore, data comparing surgical and conservative treatment can be collected. This will hopefully allow treatment recommendations for patients with LDH accompanied by a sensomotoric deficit.

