## Methods/Design

### Study design

The RECO-Study is a prospective, monocentric, randomized, controlled clinical trial. The study objective is to evaluate the improvement of sensory and motor nerve function in patients two years after either lumbar sequestrectomy (Population 1) or conservatively treated patients for LDH (Population 2), following the application of SES in the early stages of recovery (within two months after diagnosis or treatment decision). As the functional status, as well as sensory recovery parameters, are known to be assessed after two years of follow-up, this specific endpoint was also chosen for our study [12, 38, 41]. Randomization will be performed for application of electrical stimulation and therapy of recovery, but not for initial therapy of LDH. Outcome is assessed by QST [25], two-point discrimination testing (2PD) [32], manual muscle testing (MMT) [16], magnetic resonance imaging (MRI) parameters [18, 24], and by validated scales and scores. These include the Oswestry Disability Index (ODI) [6] and the Core Outcome Measures Index (COMI) [4] that are applied to assess the domains pain, back-specific function, work disability, and patient satisfaction. The generic health status is investigated with the EQ-5D [5]. Neuropathic pain components are identified with the painDETECT questionnaire (PD-Q) [10]. The severity of depression is assessed by the Beck Depression Inventory (BDI) [29]. Moreover, neurological status, muscle force, pain medication usage, and blood samples (CRP, TNFα, IL-1β, IL-6) [17, 35] will be evaluated. Furthermore, the timed up and go test (TUG) [13] will be performed. Primary and secondary outcome parameters are outlined in Additional file 1: Table S1.

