### Study population

The study protocol aims to include patients who suffer from a LDH with radiculopathy and a sensomotoric nerve dysfunction. Patients are naturally divided into two groups, whether their individual condition qualifies them for lumbar sequestrectomy according to the guidelines of DGNC and DGOOC (Population 1) or for initial conservative treatment (Population 2). If conservative treatment (including usage of pain medication according to the WHO level scheme and physiotherapy for all, and epidural steroid injection in exceptional cases, like therapy refractory radicular pain without motor deficit) is inefficient for more than six weeks, or if patients suffer from a severe paresis, surgical treatment will be performed. Population 2 is thus allowed to cross over to Population 1. Surgically treated patients will receive postoperative pain therapy according to the WHO level scheme but no additional active physiotherapy in the first eight weeks after surgery, except SES. Radiculopathy is defined as pain, paresis (muscle strength grade 4 or less), or a sensory dysfunction in a specific nerve root distribution area L3 to S1. Additionally, a radiologically determined pathology at treatment level investigated by MRI needs to correlate to the clinical symptoms. To minimize risk factors for an unfavorable outcome, patients with significant co-morbidities (see inclusion and exclusion criteria in, Additional file 2: Table S2) need to be excluded, as this may mask a difference in treatment efficacy. Informed consent is obtained from each participant.

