### Surface electrical stimulation

After a guideline-dependent decision of the initial treatment for LDH, patients will be randomized into two groups, respectively, in a 1:1 allocation ratio: 20 patients (50%) in Population 1 and 20 patients (50%) in Population 2 will receive SES, whereas the other half will follow standardized treatment algorithms adjusted to the initially chosen therapy for LDH (see Additional file 3: Figure S1).

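### The Discussion expects the trial to identify the superior treatment, surgical or conservative, but that comparison is not randomised and is confounded by indication

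*Protocol article*

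**What the plan says.** The stated objective, the sample size and the primary analysis all concern SES against no SES. The Study design section is open about what is allocated at random: "Randomization will be performed for application of electrical stimulation and therapy of recovery, but not for initial therapy of LDH". The section on surface electrical stimulation gives the order of events: "After a guideline-dependent decision of the initial treatment for LDH, patients will be randomized into two groups".

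Under Study population, patients fall into Population 1 (surgical) or Population 2 (conservative) according to "whether their individual condition qualifies them for lumbar sequestrectomy according to the guidelines of DGNC and DGOOC". If conservative care has not worked for more than six weeks, "or if patients suffer from a severe paresis, surgical treatment will be performed". Movement from Population 2 to Population 1 is allowed.

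The Discussion then goes beyond the SES question. It reasons that patients compare well because their treatment is standardised, and adds: "All quantitative values can be compared between the initial treatment groups (conservative or operative"). It closes by expecting the data on both forms of management "to prospectively identify a superior treatment method for symptomatic LDH". The abstract is more modest and says only that "data comparing surgical and conservative treatment can be collected".

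**The concern.** Naming a superior treatment is a causal conclusion about surgery versus conservative care. It needs two groups that would have recovered alike under the same treatment. Here the groups are formed by the clinical features that decide who is operated on, and the article treats those features as prognostic. Standardised delivery of treatment within each population does not make the populations alike at entry.

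The Discussion's limitations name crossover and SES exposure before a later operation. They do not name selection by indication. A reader who takes the closing sentence at face value could read a difference of either sign as an effect of the initial treatment, when part or all of it reflects who was sent to surgery.

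**Working it through.** The point rests on no figure in the plan, so the main check sets the sections side by side.

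1. **Allocation.** SES is randomised and initial therapy is not (Study design). The treatment decision comes before randomisation (Surface electrical stimulation). The 1:1 ratio therefore balances SES within each population and does nothing to balance the populations against each other.
2. **Selection.** Individual condition and guideline indication decide the population. Severe paresis or failed conservative care leads to surgery (Study population).
3. **Prognosis.** The Background lists gender, pain, and the duration and severity of paresis as influences on recovery. Steps 2 and 3 share a factor, severity of paresis, that both selects treatment and predicts outcome. That is confounding by indication on the document's own account.
4. **Crossover.** It runs one way, conservative to surgical, and the Discussion expects it. If crossovers are kept where they entered, the treatment contrast is diluted. If they are moved to the surgical group, those who responded to conservative care remain in Population 2. Neither choice removes the selection in step 2.
5. **Co-treatment.** Every conservative patient receives physiotherapy, while surgical patients receive no active physiotherapy for eight weeks other than SES. Even between balanced groups, a difference could not be attributed to the operation alone.

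**Illustration of scale (assumed gap).** The document gives no baseline imbalance, so a range is shown.

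- Inputs: 40 surgical and 40 conservative patients (abstract), a two-sided 0.05 test, no true treatment difference, and a prognostic gap of δ SD between populations.
- Two-sample t-test: df = 2 × 40 − 2 = 78; noncentrality λ = δ × √(40/2) = 4.472δ.
- Probability of a significant result = 1 − F(c; 78, λ) + F(−c; 78, λ), where F is the noncentral t distribution function and c the 97.5% point of t with 78 df.

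| Assumed gap δ (SD) | λ, 40 vs 40 | Significant, 40 vs 40 | Significant, 32 vs 32 |
|---|---|---|---|
| 0 | 0 | 5% | 5% |
| 0.25 | 1.118 | 19.7% | 16.6% |
| 0.50 | 2.236 | 59.8% | 50.4% |
| 0.75 | 3.354 | 91.2% | 84.0% |

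The last column uses λ = δ × √(32/2) = 4δ with 62 df. It applies the 20% loss that serves as the upper limit in the sample size section (40 × 0.8 = 32). For scale, the SES effect used in planning is 3.4/6.8 = 0.5 SD.

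**The case against.** The strongest reply is that nothing in the planned analysis depends on the sentence. The objective, sample size and primary test all serve SES, the non-random choice of initial therapy is disclosed, and the sentence is a closing expectation. That stands, and it makes this a fault in what the article says it will conclude. It does not remove the fault, because an expected conclusion that the design cannot support should not remain in a protocol.

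Several stronger readings are tempting, and the document does not support them:

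- **An unadjusted comparison or a superiority test is planned.** The Discussion says only that values can be compared. The method may be in the analysis plan, which is not shown.
- **Crossovers will be counted as surgical.** Study population speaks of crossing over to Population 1, but the Discussion compares initial treatment groups. The grouping is not settled.
- **Treatment recommendations will rest on surgery versus conservative care.** The abstract's hope for recommendations follows its mention of that comparison but can also refer to the SES results. In the main Discussion it follows from factors that influence recovery. Both statements are hedged.
- **Different physiotherapy is itself a bias.** It can be seen as part of two management strategies. It then limits attribution to surgery and does not confound a comparison of strategies.
- **The false-positive rate is about 60%.** That is one row of an assumed range. A gap of 0.5 SD has no source in the document.

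Adjustment in an unseen analysis plan could reduce measured confounding. It would not turn a contrast selected by guideline into evidence of superiority.

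**Conclusion.** The concern holds as a mismatch between conclusion and design. The surgical versus conservative contrast is confounded by indication and complicated by one-way crossover, and differing physiotherapy limits attribution to surgery. It cannot identify a superior treatment, and standardised treatment does not make the two populations comparable.

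The direction and size of the bias are unknown. The 20% to 91% range depends wholly on an assumed prognostic gap of 0.25 to 0.75 SD, full follow-up of 40 versus 40, and a simple two-sample test that the article does not specify. It shows only that a moderate gap would be enough to mislead.

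A reader might infer that the randomised result is also undermined. It is not: SES is allocated at random within each population, so selection into surgery does not bias that comparison.

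**What to change.** - Delete the expectation in the Discussion that the trial will identify a superior treatment. Withdraw the inference of comparability from standardised treatment where it is applied to the two populations.
- State that surgical versus conservative results are observational and exploratory.
- Group patients by initial treatment at entry for this comparison, and adjust for baseline severity: CDT, muscle strength grade and pain. Report estimates with 95% confidence intervals and draw no conclusion on superiority.
- Add selection by indication and differing co-treatment to the limitations, next to crossover.

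**Cost.** The claim and the limitations need only a change of wording. The adjusted comparison needs a short specification in the analysis plan, if it is not already there. It uses measures the article already lists, so no new data are needed provided the pre-treatment examination covers them. No treatment rule, sample size or randomised analysis changes. The work on prognostic factors for recovery can continue, since observational data can inform it.

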### Trial status

Recruitment is planned to be started in October 2017, as soon as the authority’s clearance is available.

## Abbreviations

ANCOVA: Analysis of covariance
DGNC: German Society of Neurosurgery
DGOOC: German Society of Orthopaedics and Orthopaedic Surgery
EMG: Electromyography
MRC: Medical Research Council
MRI: Magnetic resonance imaging
WHO: World Health Organization
